## Abstract

**Background:**

Evidence supporting the use of statin therapy to reduce stroke recurrence and cardiovascular events in acute cardioembolic stroke (CES) patients without atherosclerosis is limited. Past observational studies have been hampered by selection bias and unmeasured confounding factors. This study aims to investigate the potential benefits of statin therapy in acute CES patients without established indications through a registry-based, randomized clinical trial.

**Methods:**

This is a registry-based, multicenter, prospective, randomized, open-label, blinded endpoint (PROBE) study designed to evaluate the efficacy and safety of statin therapy in acute CES patients without established indications for statin use. Patients will be randomly assigned (1:1) to either statin users or non-users, with statin users receiving atorvastatin at a dose of 10 mg or higher throughout the study period. We plan to recruit 1036 participants to detect a relative risk reduction of 43% with 80% power and a two-sided alpha error of 0.05, accounting for a 10% loss to follow-up. The primary outcome is the occurrence of a major clinical event, defined as a composite of stroke recurrence, myocardial infarction, and all-cause mortality within 3 months after the index stroke. The secondary efficacy outcomes include (1) stroke recurrence, (2) all-cause mortality, (3) vascular death, and (4) major vascular events.

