### Sample size estimates

To estimate event rates, a simulation study was performed using the CRCS-K-NIH registry database to closely reflect the characteristics of the trial’s target population. Data from a total of 5,261 patients who met the study’s selection criteria between April 2008 and November 2019 were extracted from the registry. During this period, the registry included 72,796 patients, of whom 65,801 had ischemic stroke, 63,340 presented within 7 days of symptom onset, 13,853 had cardioembolic stroke, 5579 did not receive statin therapy, and 5261 arrived at the hospital within 2 days of symptom onset.

The timing of randomization was based on a recent Korean study which showed that a significant number of major vascular events associated with statin therapy occur within the first month, particularly within the first 7 days [10]. To account for clinical feasibility, five randomization scenarios were developed (Supplemental Table 4), and scenario #3 was selected for simulation. Major event rates within 90 days between the treatment and control groups were compared for each of the 10 simulated datasets (Supplemental Table 5).

Considering that stroke severity is closely related to clinical outcomes, patients were categorized into three groups based on the National Institutes of Health Stroke Scale scores: mild (0–4), moderate (5–10), and severe (> 10). The estimated between-group differences in 90-day event rates were 2% for the mild group, 5% for the moderate group, and 25% for the severe group. These findings suggest that the overall 17% risk difference may have been driven disproportionately by the severe group, where indication bias and unmeasured confounders could have affected statin use and outcomes.

To minimize this potential bias, we based our sample size calculation on the moderate severity group. Using event rates of 7% in statin users and 12% in non-users (hazard ratio of 0.568), we estimated that 1036 patients and 99 events would provide 80% power to detect a 43.2% relative risk reduction at a two-sided alpha of 0.05, based on a group sequential log-rank test. An interim analysis at 50% of the information time is conducted using the O’Brian-Flemming type alpha spending function. Accounting for a 10% loss to follow-up, we plan to enroll 1152 patients under the intention-to-treat (ITT) principle.

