## Trial status

The latest version of the trial protocol is 1.6, dated 23 December 2024. The trial began recruiting patients on 1 December 2022 and is actively enrolling. As of May 31, 2025, 375 patients (36.2% of the planned sample size) have been enrolled.

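### The Abstract presents 1036 as the recruitment target after 10% loss, but the sample-size section derives 1036 before loss and 1152 after it, and the Trial status percentage also rests on 1036

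*Protocol article*

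**What the plan says.** The document describes the planned size in three places.

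- **Abstract, Methods:** "We plan to recruit 1036 participants to detect a relative risk reduction of 43% with 80% power", with a "two-sided alpha error of 0.05, accounting for a 10% loss to follow-up". Read plainly, 1036 is the number to recruit and already contains the loss allowance.
- **Methods, Sample size estimates:** the assumptions are stated as "Using event rates of 7% in statin users and 12% in non-users (hazard ratio of 0.568"), followed by "we estimated that 1036 patients and 99 events would provide 80% power to detect a 43.2% relative risk reduction". The calculation is for a log-rank test in a group sequential design with two-sided alpha 0.05. One interim look at 50% information uses O'Brien-Fleming-type spending. The loss allowance is a separate last step: "Accounting for a 10% loss to follow-up, we plan to enroll 1152 patients under the intention-to-treat (ITT) principle".
- **Trial status:** as of 31 May 2025, "375 patients (36.2% of the planned sample size) have been enrolled". This section prints no target and mentions no loss allowance.

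**The concern.** The Abstract and the Sample size estimates section both state an enrolment plan, and both claim to include the same 10% loss, yet one says 1036 and the other 1152. They cannot both be right. The Trial status percentage shows that the smaller number is used in a second place, so the conflict goes beyond one sentence in the Abstract.

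The trial is still enrolling, so the number taken as the target affects when recruitment would be considered complete and how progress is reported. If the smaller number were used and the assumed loss occurred, the trial would have fewer than the 99 events on which its 80% power rests.

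**Working it through.** **Inputs.** From Sample size estimates: 90-day event rates of 7% and 12%, two-sided alpha 0.05, power 80%, one interim look at 50% information with O'Brien-Fleming-type spending, and 10% loss. From the Abstract: 1:1 allocation. From Trial status: 375 enrolled, 36.2%.

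**1. Reproduce the plan's figures.**
- Hazard ratio: ln(0.93)/ln(0.88) = 0.5677, which rounds to the stated 0.568.
- Events, fixed design (Schoenfeld): 4 × (1.960 + 0.842)² / (ln HR)² = about 98.
- The two-look design has bounds 2.963 and 1.969 and an inflation factor of 1.0037. It needs 98.3 events (unrounded HR) to 98.5 events (HR 0.568), so 99.
- Patients: the mean event rate is (7% + 12%)/2 = 9.5%. 98.3/0.095 = 1035 and 99/0.095 = 1042, and the plan's 1036 lies in this range. Conversely, 1036 × 0.095 = 98.4 events, with power 80.0%.
- Loss: 1036/0.9 = 1151.1, rounded up to 1152.

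The Sample size estimates section is therefore internally correct, and 1036 is the number before loss. Of the formulas tried, only this one returns 99 and 1036. Freedman's formula gives 104 events, and a comparison of two proportions gives 1078 patients (1156 with continuity correction).

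**2. Find the denominator in Trial status.**
- 375/1036 = 36.2%.
- 375/1152 = 32.6%.

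Of the two stated sizes, only 1036 gives the printed percentage.

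**3. Power if enrolment stopped at 1036 and 10% were lost.** The drift is √(events/4) × |ln HR|. Power is given for the two-look design, with the fixed design in brackets, at the unrounded HR.

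| Case | Expected events | Power |
|---|---|---|
| 1036 enrolled, lost patients contribute no events | 1036 × 0.90 × 0.095 = 88.6 | 75.8% (75.9%) |
| 1036 enrolled, half of the lost patients' risk observed (assumption) | 1036 × 0.95 × 0.095 = 93.5 | 78.0% (78.2%) |
| 1152 enrolled, lost patients contribute no events | 1152 × 0.90 × 0.095 = 98.5 | 80.1% (80.2%) |

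Using the rounded HR of 0.568 changes these by about 0.1 percentage point. The Freedman and two-proportion formulas give about 73.5-74% in the first case. They also give only about 78% with all 1036 observed, so they are not the plan's method, and their fall is of similar size.

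**4. The effect label.** 1 − 0.568 = 43.2% is the reduction in hazard. The relative risk reduction from 12% to 7% is 1 − 7/12 = 41.7%.

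**The case against.** The strongest reply is that this is a drafting slip. The only section that sets out the design states 1152 without ambiguity, its derivation is correct, and the full protocol (version 1.6) is not shown. An Abstract sentence and a status percentage that share one wrong number do not prove a decision to close at 1036. This stands. A reader might infer that the trial is being run to the uninflated number, but the document does not establish that. Trial status does not print 1036 or mention loss; its denominator is a back-calculation.

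A reader might also take 76% as the power the trial will have. It is the lower end of a range, and it needs two conditions: enrolment stops at 1036, and lost patients contribute nothing. The second condition is pessimistic. The primary test is a log-rank test, which uses follow-up to censoring. Outcomes are collected in hospital as well as at 3 months, and the sample-size section itself notes that many events come early. Patients lost later may already have passed through much of their risk.

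Two further routes could preserve power. The Statistical analysis section allows sample-size re-estimation when interim conditional power is 50-80%. A final analysis that waited for 99 events would keep about 80%. However, the document ties only the interim analysis to an event count (50) and does not say that the final analysis waits for 99.

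On the effect label, the hazard ratio and both event rates stand beside the 43.2%, so the assumption used is clear and no sample size changes.

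None of this removes the contradiction. The Abstract's claim that 1036 includes the loss allowance remains false against the document's own derivation. What the monitoring board works from and what the trial registry says cannot be judged from this document, so no error is claimed there.

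**Conclusion.** The point holds. As written, the Abstract attaches the 10% loss allowance to a number that does not contain it. The enrolment target derived in the document is 1152, which is 116 more than the Abstract states. The Trial status percentage uses the same uninflated number; on the derived target, progress is 32.6% rather than 36.2%.

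The effect on power is conditional. If enrolment stopped at 1036 and 10% were lost, power would be about 76% with no events from lost patients, about 78% with half their risk observed, and would approach 80% only if loss cost almost no events. These figures rest on the plan's own event rates, proportional hazards, a 9.5% mean event rate and the Schoenfeld approximation. If 1152 are enrolled, the stated 80% stands.

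The design calculation itself needs no correction. The target should nevertheless be settled while recruitment is open. The 43.2% label is a minor wording matter.

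**What to change.** - **Abstract:** give 1152 as the number to recruit, allowing for 10% loss, with 1036 (99 events) as the number required before loss.
- **Trial status:** report 375/1152 = 32.6%.
- **If 1036 really is the enrolment target:** change the Sample size estimates section to match, remove the claim that 80% power allows for 10% loss, and restate power as about 76-80%, depending on how much follow-up is observed before loss.
- **Effect label:** in the Abstract and Sample size estimates, call 43% and 43.2% a hazard reduction. If a relative risk reduction is wanted, give 41.7%.

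The cost is a few corrected figures and words. If 1152 is the target in the full protocol, the design does not change.

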**Discussion:**

This study will assist stroke physicians in determining the appropriate use of statin therapy for acute CES patients who do not have guideline-based indications.

**Trial registration:**

CRIS Registration Number: KCT0006806. Registered on November 29, 2021. URL: https://cris.nih.go.kr/cris

**Supplementary Information:**

The online version contains supplementary material available at 10.1186/s13063-025-09097-x.

## Background

Cardioembolic stroke (CES) is one of the most severe and fatal subtypes of ischemic stroke, often resulting in high early mortality and poor long-term outcomes [1, 2]. However, there remains a lack of evidence regarding optimal secondary prevention strategies, particularly for patients who do not meet current statin eligibility criteria. Despite advances in stroke prevention and treatment, optimal strategies for secondary prevention in CES remain unclear—particularly for patients who fall outside current guideline-based statin eligibility. While high-intensity statins have shown benefit in reducing recurrent events among patients with recent ischemic stroke or transient ischemic attack (TIA) without known coronary heart disease (CHD) [3], the role of statin therapy in CES patients without a clear indication remains uncertain and under-investigated.

Current guidelines remain uncertain regarding the benefits of statin use in patients without established atherosclerotic disease [4]. The inconsistency between guidelines and related performance measures for statin use in ischemic stroke patients further complicates the issues, potentially leading to the inappropriate use of statins in this population [4–7]. For patients with cardioembolic stroke (CES), evidence regarding statin use is particularly lacking, especially in those without concomitant atherosclerosis. The Stroke Prevention by Aggressive Reduction in Cholesterol Levels (SPARCL) trial excluded patients with cardiac sources of embolism (e.g. CHD, atrial fibrillation, prosthetic heart valve, significant mitral stenosis, and sinus node dysfunction) [3]. Observational studies have suggested that statin therapy may reduce mortality and vascular events in CES patients [8, 9]. However, these studies have important limitations. One included patients with conditions known to benefit from statins, such as aortic atheroma or coronary artery disease [9], potentially introducing selection bias. Another did not clearly report whether patients with established indications for statin therapy were excluded [8], making it difficult to isolate the effect of statin in CES patients with such indications.

In a recent study using the nationwide, multicenter, prospective stroke registry in Korea (Clinical Research Collaboration in Korea-National Institute of Health; CRCS-K-NIH registry), statin therapy was associated with decreased mortality and vascular events in patients with acute CES, even though these patients had no established indication for statin therapy according to current guidelines [10]. Despite these findings, the retrospective design of the study, the presence of residual or unmeasured confounding factors, and inherent biases limit the generalizability of its conclusions.

This study aims to evaluate the potential benefits of statin therapy in reducing major clinical events within 90 days among patients with acute cardioembolic stroke who do not meet current guideline-based indications for statin use.

## Methods

### Study design

The Statin Therapy for the Prevention of Major Clinical Events in Acute CardioEmbolic Stroke Patients without a Definite Indication for Statins (STACE) Trial is a registry-based, multicenter, prospective, randomized, open-label, blinded end-point (PROBE) study. This study aims to evaluate the efficacy and safety of statin therapy in acute CES patients who have no established indication for statin therapy according to current guidelines within a registry-based randomized clinical trial (RRCT) setting.

The RRCT design offers several advantages in clinical research. By utilizing real-world patient data, it ensures diverse patient representation, thereby enhancing the generalizability of the findings [11]. Integrating randomization within registry frameworks increases trial efficiency, minimizes recruitment challenges, and reduces administrative costs. Additionally, since registry data are collected as part of routine clinical practice, the effort required to capture outcomes is reduced compared to traditional RCTs. Overall, the registry-based RCT approach provides valuable insights into treatment effectiveness and safety in real-world settings, offering a cost-effective and efficient method for conducting clinical research.

This RRCT utilizes the CRCS-K-NIH registry for patient enrollment, randomization, outcome assessment, and follow-up. Study timeline conforming to the SPIRIT guidelines is in Fig. 1. Detailed information about the CRCS-K-NIH registry was published previously [12] and is described in the Supplemental Methods.

**Fig. 1 Fig1:**
[figure not shown]
STACE study timeline

### Patient population—inclusion and exclusion criteria

Adults (age of 19 or older) with acute ischemic stroke (within 4 days of symptom onset) of the cardioembolic subtype, as classified by a modified Trial of Org 10,172 in Acute Stroke Treatment classification system [13], are eligible for the study. High-risk cardioembolic sources [13] are listed in the Supplemental Table 1. Patients who were taking statins on a regular basis prior to the index stroke will not be included in the study.

Patients who do not meet any of the criteria for the four statin benefit groups, as defined by the 2013 American College of Cardiology (ACC)/American Heart Association (AHA) Cholesterol guidelines, are eligible for this trial (Fig. 2) [4]. The four statin benefit groups are summarized as follows: (1) individuals with clinical atherosclerotic cardiovascular disease (ASCVD); (2) individuals with elevated low-density lipoprotein-cholesterol (LDL-C) levels ≥ 190 mg/dL; (3) individuals aged 40–75 years with diabetes and LDL-C levels between 70 and 189 mg/dL; or (4) individuals without diabetes, aged 40–75 years, with LDL-C levels between 70 and 189 mg/dL and an estimated 10-year ASCVD risk of 7.5% or higher. The determination of statin indications will be based on information obtained at the time of hospitalization for the index stroke.

**Fig. 2 Fig2:**
[figure not shown]
Study flowchart

Patients with any of the following criteria will be excluded from the study: (1) refusal to participate in the study, (2) abnormal liver function test (aspartate transaminase or alanine transaminase > 200 IU/L), (3) contraindications to or allergies to statins, (4) pregnancy or breast-feeding, (5) participation in another clinical trial involving anti-dyslipidemic agents, (6) a life expectancy of 6 months or less, or (7) use of contraindicated medications, such as other statins, proprotein convertase subtilisin/kexin type 9 inhibitors, cyclosporine, or fibrates.

After verification of the inclusion and exclusion criteria, written informed consent will be obtained from the patients. Patients will be informed about the purpose, process, and the expected benefit and harm of participation.

### Randomization

Once a patient provides informed consent to participate in the study, they will be randomly assigned to either the statin user group or the statin non-user group through the Interactive Web Response System (IWRS) integrated within the CRCS-K-NIH/STACE registry database. Randomization will be conducted using permuted block randomization with a pre-specified block size, stratified by participating centers to ensure balanced allocation across sites. The randomization sequence will be pre-generated by an independent biostatistician, and randomization will occur within four calendar days of symptom onset.

Although the trial is open-label, allocation concealment was strictly maintained. The pre-generated randomization sequence was embedded in a centralized IWRS implemented on the CRCS-K-NIH registry platform. This system ensures that treatment assignments remained concealed from both investigators and participants until the point of allocation, thereby minimizing selection bias and preserving the integrity of the randomization process.

In addition, patients who meet the eligibility criteria but decline participation will be monitored and recorded within the registry database; these individuals will comprise the non-RRCT analysis population, as defined in the Statistical Analysis section.

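### As worded, one block size per centre in an open-label trial makes the end of each block predictable once the size is known, so the claim of strict concealment is too strong

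*Protocol article*

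**What the plan says.** All of this stands in the protocol article, mostly under Randomization.

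- **Scheme:** "permuted block randomization with a pre-specified block size", "stratified by participating centers to ensure balanced allocation across sites". The abstract gives the ratio: "Patients will be randomly assigned (1:1) to either statin users or non-users".
- **Generation:** "The randomization sequence will be pre-generated by an independent biostatistician". The list sits in a central web response system on the registry platform.
- **Concealment:** "Although the trial is open-label, allocation concealment was strictly maintained". The system is said to ensure that "treatment assignments remained concealed from both investigators and participants until the point of allocation", and this is credited with minimising selection bias.
- **Non-participants:** "patients who meet the eligibility criteria but decline participation will be monitored and recorded within the registry database".

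The article does not give the block size, say that sizes vary, or say whether sites are told the size. Sample size estimates says that stroke severity is closely related to clinical outcome. Severity is not a stratification factor.

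**The concern.** A 1:1 permuted block must end in balance. Once one arm has used up its places in a block, every remaining place belongs to the other arm. In an open-label trial with blocks within centre, staff see all earlier assignments on their own list. Someone who knows the block size and keeps count therefore knows the end of each block before the next patient consents.

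A central system protects the list from being read. It does not protect it from being worked out, so concealment until the point of allocation cannot be guaranteed by that system alone.

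What is at stake is selective enrolment. If staff know the next arm, the decision to approach a patient can depend on it. Because severity bears on outcome and is not balanced by design, patients chosen in this way could differ between arms before treatment starts. Blinded endpoint assessment offers no protection, since the bias enters before any endpoint is assessed.

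**Working it through.** **The plan's own figures.** The article gives no figure for predictability, so there is none to reproduce. The figure that bears on a mid-trial change is enrolment under Trial status: 375 patients, stated as 36.2% of the planned sample. 375/1036 = 36.2%, which reproduces it. Against the enrolment target of 1152 under Sample size estimates, 375/1152 = 32.6%. At 31 May 2025, between 63.8% and 67.4% of allocations were therefore unused.

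**Inputs.** From the article: 1:1 ratio, one block size, centre-only strata, open-label treatment. Assumed: block sizes of 4, 6 or 8, and an observer who knows the size and the centre's full sequence. The results for fixed sizes are therefore upper bounds.

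**Certain allocations, fixed size 2n.** The expected number of certain places at the end of a block is 2n/(n+1), so the share is 1/(n+1). Check for size 4: starting with either arm, there are three equally likely patterns. In one (two of the same arm first) the last two places are certain; in the other two only the last is. The mean is (2 + 1 + 1)/3 = 4/3 of 4 places, or 33.3%.

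**Best guess, fixed size 2n.** Always guess the arm with more places left in the block. The expected success rate is 1/2 + [4^n/C(2n,n) − 1]/(4n).
- Size 4: 1/2 + (16/6 − 1)/8 = 70.8%
- Size 6: 1/2 + (64/20 − 1)/12 = 68.3%
- Size 8: 1/2 + (256/70 − 1)/16 = 66.6%

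**Randomly varied sizes.** These were simulated for centre lists of 20, 40 and 60 patients. The observer knows the possible sizes and all past allocations but not where blocks end, and always makes the most probable guess.

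| Scheme (assumed) | Certain in advance | Predictable with probability of at least 80% | Best-guess success |
|---|---|---|---|
| Fixed 4 | 33% | 33% | 71% |
| Fixed 6 | 25% | about 22-25% | 68% |
| Fixed 8 | 20% | about 18-22% | about 67% |
| Random 4, 6 | about 5.5% | about 27-29% | about 69% |
| Random 4, 6, 8 | about 2% | about 20-24% | about 67-68% |

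Pure chance is 50%. Varying the sizes removes most certain predictions. Best-guess success moves by two to three points against fixed size 4 and does not improve in any useful way on fixed 6 or 8.

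**Can an undisclosed size be inferred?** Take an observer who starts with equal weight on sizes 2, 4, 6 and 8 (an assumption) and sees one centre's allocations only. For a true size of 4, 6 or 8, the mean posterior probability on the true size is about 72-82% after 20 patients, 85-88% after 30 and 92-95% after 40. Withholding a single size therefore helps for a time only. Accrual per centre is not given, so how many centres would reach these counts is unknown.

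**The case against.** **The wording may not mean one fixed size.** The word fixed does not appear, a varied scheme is also specified in advance, and the full protocol (version 1.6) is not shown. This stands as a caution. One size is still the natural reading of the singular, and if the full protocol varies the sizes, the article describes the scheme wrongly.

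**The predictable shares are upper bounds.** They need someone who knows the size and tracks every allocation at the centre. The article does not say that sites are told it. This stands, and it means that the number of allocations actually foreseen is not established.

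**Varying the sizes does little against guessing.** This stands in full. A reader might infer that varied sizes would largely remove the opening to selective enrolment. The figures support that only for allocations known with certainty, and steering does not need certainty.

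**The severity figures do not measure prognosis.** A reader might take the 2%, 5% and 25% under Sample size estimates as a gradient of risk by severity. They are differences between statin users and non-users within severity groups, and the article itself suspects indication bias in the severe group. Only its general statement that severity is closely related to outcome can be used here.

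**The log of decliners need not hide selection.** A reader might infer that a patient held back by staff would be entered as a decliner and treated at the physician's choice. The article says only that eligible patients who decline are monitored and recorded.

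**There are partial safeguards.** Randomization must take place within four calendar days of onset, which limits holding a patient for a preferred slot. Statistical analysis plans Cox adjustment for baseline imbalance and a comparison of participants with non-participants. They help only in part: adjustment covers measured variables, and the comparison as described is not by arm.

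**Conclusion.** The point holds in a limited form. As worded, the scheme makes block ends certain in advance to anyone who knows or infers the size, and a central system does not prevent that. The assurance of strictly maintained concealment therefore goes further than the design supports. The size is at most 33%, 25% or 20% of allocations for assumed block sizes of 4, 6 or 8.

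The conclusion rests on reading the text as one size per centre and on staff being able to learn that size; the article settles neither. It does not show that selective enrolment has occurred or how large any bias would be, and a reader should not infer either. The point is worth acting on because the better method is cheap and, at the last stated count, roughly two thirds of allocations were unused.

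**What to change.** First check the full protocol. If it already varies the block sizes, correct the article's wording and nothing else is needed.

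If it does not, have the independent biostatistician generate a new centre-stratified sequence with randomly varied block sizes (for example 4, 6 and 8) for the unused allocations, and load it in the web system. Start it at a block boundary in each centre, so that no block is cut short. Withhold the sizes from sites. Replace the reference to a block size with a statement that sizes vary at random and are not disclosed, and soften the claim about concealment.

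The cost is a short amendment, a new list in the system with a managed changeover at each centre, and slightly larger transient imbalance within centres. The sample size, endpoint and analysis are unaffected. The share of allocations that can still benefit falls as enrolment proceeds.
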